### Outcomes

The primary outcome was caregiver distress, and the secondary outcomes were anxiety, depression, and negative emotions. Distress is the primary outcome, as distress contributes to the development of anxiety and other negative emotions [68]. All outcome measures were caregiver-reported outcomes assessed using psychometrically sound tools and were analyzed using the metric of change from baseline.

### Sample Size

The sample size needed to address the major aim of the study (N=150) was calculated using the Hedeker formula [69] for a repeated measures mixed effects model and included the following assumptions: a power of 0.80, correlation among 3 repeated measures of 0.5, a small Cohen *d* effect size of 0.35, and an attrition rate of 20%. These assumptions are consistent with previous studies on unpaid caregiver interventions reporting clinically meaningful changes in mental health outcomes [31,37,41,42,70].

Given that this is a pilot study, the analyses are considered exploratory in nature. Given the absence of studies testing interventions for caregivers of persons with multiple sclerosis, we will identify potential moderators a priori before testing them in the full analyses and will not test them simultaneously. As a result, we will have adequate power to detect medium to large effects using a structural equation modeling approach for our full analyses.

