### Statistical Methods

Data will be analyzed using SPSS and SAS, and all investigators, along with the statistician and data manager, will have access to the final data set. Before conducting multivariate analyses to examine group differences, we will use descriptive techniques to examine univariate characteristics and bivariate relationships among variables, covariates, and outcomes. These techniques will be based on proportions, medians, and means. We will also describe (for each variable) frequencies and measures of central tendency for all variables and assess data for violations of assumptions for all planned statistical tests. Data transformations will be used to remedy issues concerning nonlinearity or high skewness.

To address the primary outcome (distress), a linear mixed effects model will be used to test whether there is a significant difference between intervention groups in time on the caregiver outcome of distress. The linear mixed effects model will include the variables of group assignment, time, and the interaction of time by group, along with the participant-specific random intercept and slope. Intention-to-treat and per-protocol analyses will be conducted. The linear mixed effects model should be sufficient in most cases to account for missing data in the intention-to-treat analysis. Participants who provide complete data and attend three or more coaching sessions will be included in the per-protocol analysis. We will also explore the influence of COVID-19 anxiety and website usage as covariates and test for moderation by multiple sclerosis disability, race, ethnicity, rural versus urban location of the caregiver, caregiver COVID-19 positive or negative status, whether the caregiver is local or distant from the person with multiple sclerosis, and socioeconomic status. The analytic approach for the secondary outcomes (anxiety, depression, and negative emotions) will be identical to that used for examining the primary outcome of the study.

The study results will be communicated to the participants via email and publication in patient-focused venues, such as the National Multiple Sclerosis Society’s website [78]. In addition, the results will be reported to the sponsor in the final report and via publications and presentations to health care providers in appropriate journals (eg, the *Multiple Sclerosis Journal* and the *Journal of Neurological Sciences*) and conferences.

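### The 0.80 power stated for N=150 does not hold for the planned time-by-group test of distress, whose power is about 0.5 for the linear slope

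*Protocol article*

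**What the plan says.** The Sample Size section attributes the total of 150 to a published formula "for a repeated measures mixed effects model and included the following assumptions". The listed inputs are "a power of 0.80, correlation among 3 repeated measures of 0.5", a Cohen d of 0.35 and 20% attrition. The list contains no alpha and no sidedness. It does not say whether d is a difference at one visit, a difference averaged over visits, or a difference in change. The same section calls the trial a pilot and its analyses exploratory.

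The Statistical Methods section fixes the primary analysis of distress: "The linear mixed effects model will include the variables of group assignment, time, and the interaction of time by group", together with a random intercept and a random slope for each participant. The Objectives section expects a larger reduction over time with coaching, across baseline, 6 weeks and 12 weeks. The Outcomes section says the measures are analysed as change from baseline. Together these make the target a group difference in change.

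**The concern.** A power figure belongs to one test of one contrast. With a correlation of 0.5, the variance of a difference in change is larger than that of a baseline-adjusted follow-up mean. It is also larger than that of an average over all three visits. A sample size that suits one of those contrasts can therefore fall well short for the time-by-group term.

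What is at stake is how a non-significant result on distress would be read. The Conclusions section expects the results to settle whether either or both interventions give clinically meaningful improvement. A test with a power of about one half cannot bear that weight, and a reader who relies on the stated 0.80 would not know it.

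**Working it through.** **Inputs from the article.** N=150, power 0.80, d=0.35, three visits with correlation 0.5, attrition 20%.

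**Assumptions, because the article is silent.** Two-sided 5% (one-sided 5% also tried), 1:1 allocation (75 per arm), compound symmetry, unit variance at each visit, and d as the standardized group difference in change. At correlation 0.5 the SD of a change score equals the raw SD, so standardizing by either gives the same d.

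**Formulas.** For a contrast with per-person variance f, n per arm = 2(z_alpha + 0.8416)² f / 0.35². Power with m per arm is Φ(0.35 / √(2f/m) − z_alpha). The value of z_alpha is 1.96 two-sided and 1.645 one-sided.

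The variances under correlation 0.5 are:
- average of all three visits: (1 + 2×0.5)/3 = 0.667
- linear slope, or week-12 change: 2(1 − 0.5) = 1.0
- mean of weeks 6 and 12 minus baseline: 1 + 0.75 − 2×0.5 = 0.75
- mean of weeks 6 and 12, baseline-constrained: 0.75 − 0.5² = 0.5

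**Trying to reproduce 150 (two-sided 5%, attrition as division by 0.8).**
- Three-visit average: 85.4 per arm, 171 in total, 214 after attrition.
- Linear slope: 128.1 per arm, 256, then 320.
- Mean follow-up change: 96.1 per arm, 192, then 240.
- Baseline-constrained follow-up mean: 64.1 per arm, 128, then 160.

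None gives 150. Two routes come close:
- A one-sided 5% test of the three-visit average needs 67.3 per arm, or 134.6 in total. Counting the 20% final loss as 10% on average gives 134.6/0.9 = 149.5.
- The two-sided baseline-constrained follow-up mean has power 0.77-0.81 at N=150.

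Neither is the time-by-group test.

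**Power at N=150.** The first figure in each cell takes 20% as lost entirely (60 per arm). The second takes dropout of 10% by week 6 and 20% by week 12, with partial data used.

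| Contrast | Two-sided 5% | One-sided 5% |
|---|---|---|
| Linear time-by-group slope | 0.48 / 0.51 | 0.61 / 0.63 |
| Mean follow-up minus baseline | 0.60 / 0.65 | 0.72 / 0.76 |
| 2-df interaction, effect growing linearly | 0.39 / 0.41 | not applicable |
| 2-df interaction, constant effect after baseline | 0.50 / 0.55 | not applicable |

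Worked example for the slope: √(2×1.0/60) = 0.1826; 0.35/0.1826 = 1.917; Φ(1.917 − 1.96) = 0.48.

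The 2-df rows use a noncentral chi-square. With 60 per arm the noncentrality is 30×0.35² = 3.68 for a linear effect and 30×0.35²/0.75 = 4.90 for a constant one.

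**Sensitivity.**
- If all the loss falls after week 6, mean-change power is 0.67 two-sided and 0.78 one-sided.
- With no attrition at all, two-sided power is 0.47-0.70 across the time-by-group readings.
- If the correlation decays with distance (first-order autoregressive, 0.5 between adjacent visits), power for the week-12 change falls to 0.35 with 60 per arm and 0.42 with 75.

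**Effect detectable with 80% power (two-sided).** With 60 per arm, 2.8016×√(2/60) = 0.51 for the slope and 2.8016×√(1.5/60) = 0.44 for the mean change. With gradual dropout these are about 0.50 and 0.42.

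**The case against.** The strongest counter-argument is that no arithmetic error has been shown. A reader might infer that the correct answer was 171 before attrition and 214 after it, so that 150 is a miscalculation. The article does not support that. Those figures need a two-sided 5% level and a time-averaged contrast, neither of which it states. The hypothesis is directional, and a one-sided time-averaged calculation with 10% average loss returns 149.5. The figure of 150 may be a correct answer to a different question. This objection stands, and it limits the point to a mismatch between the sized contrast and the planned test.

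The meaning of d is also open. If 0.35 were a per-visit increment reaching 0.70 at week 12, slope power with 60 per arm would be 0.97. The text does not say this, and it calls 0.35 a small effect.

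The three readings of the interaction should not be merged into one range. The random slope points to linear time and hence to the slope figures. The 2-df and mean-change figures apply only if time is categorical or a specific contrast is chosen.

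Finally, the trial is labelled an exploratory pilot meant to guide larger testing. That lessens the harm, and the article nowhere says that a null result will count against coaching. It does not make the stated power true.

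**Conclusion.** The point holds in this form: the stated 0.80 is not delivered for the time-by-group test on any reading of the listed inputs that takes d as the group difference in change. On the reading the model most directly implies, the linear slope, power is about one half. The exact figures rest on the assumptions listed above. The shortfall itself survives a switch to one-sided 5%, and at two-sided 5% it survives the removal of attrition altogether. Compound symmetry is kinder to the plan than the decaying correlation tried. The most plausible explanation is that the trial was sized for a time-averaged or baseline-adjusted contrast, but the article does not show which.

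**What to change.** Keep N=150 and rewrite the sample-size paragraph. State alpha, sidedness, the contrast that d refers to and the assumed attrition pattern. Then give the power of the planned time-by-group test. On the assumptions used here that is about 0.5 for the linear slope, with a detectable d of about 0.50. If mean follow-up change is the intended contrast, power is about 0.60-0.65, with a detectable d of about 0.42-0.44. This costs only wording and needs no further participants, but the stated power becomes less favourable.

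Alternatively, the sponsor could make the baseline-constrained mean of weeks 6 and 12 the primary contrast, with power of about 0.77-0.81. That changes the primary analysis of a trial that had already enrolled 66 participants by May 2021. It should be documented as an amendment before outcome data are examined, not presented as a clarification.

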### Study Instruments

All tools were selected based on psychometric properties, clinical applicability, and low participant burden. When possible, tools from the National Institute of Health Toolkit were used.

The *overall negative emotional state* was measured using the Depression Anxiety Stress Scale-42 [71]. This instrument consists of 42 statements representing negative emotional states of depression, anxiety, or stress (eg, “I found it hard to wind down” and “I felt sad and depressed”) during a 7-day recall period. The Depression Anxiety Stress Scale-42 uses a 4-point Likert scale ranging from 0 to 3, with higher scores representing a greater amount of time experiencing each statement of negative emotion (eg, 3=applied to me most of the time). Three subscale scores (depression, anxiety, and stress) were computed, and all items were summed to compute a total composite negative emotion state score. The total composite score will be used for analytic purposes, with higher scores representing a greater amount of time associated with overall negative emotions. The tool has excellent reliability and validity, with Cronbach α ranging from .88 to .94 [71], indicating that the items are homogeneous and measure a single construct.

*Anxiety* and *depression* were measured using the short-version Patient-Reported Outcomes Measurement Information System (PROMIS) instruments PROMIS-Anxiety and PROMIS-Depression, each of which has excellent psychometric properties [72]. The instruments consist of four items, use a 7-day recall period, and use a 5-point Likert scale ranging from 1 to 5, with higher scores representing more of the domain (anxiety or depression). Raw scores are converted to standardized T-scores for analysis following the PROMIS guidelines (mean 50, SD 10). Higher scores indicate greater levels of either anxiety or depression. Cutoff scores that classify scores as normal, mild, moderate, or severe are validated [70,73].

*Distress* was measured using the National Comprehensive Cancer Network distress thermometer tool. This tool is a single-item, self-report measure of psychological distress and has excellent psychometric properties for caregivers [74]. Participants rated their distress in the past 7 days using an 11-point visual analog scale ranging from 0 (no distress) to 10 (extreme distress), with higher scores indicating higher levels of distress. Scores ≥4 represent clinically elevated levels of distress for caregivers [75,76]. The use of the distress thermometer will allow us to examine its applicability within the caregiver of persons with multiple sclerosis population and compare our caregiver sample and other caregiver groups.

### Data Collection

At study enrollment, a web-based survey within REDCap was used to obtain demographic information and baseline outcome measures (negative emotions, anxiety, depression, and distress). The same measures and procedures are used 6 weeks later (the end of the intervention period) and once more 6 weeks later (to assess ongoing effects). Caregivers in both study arms answered the same survey questions. We found that participants completed the measures in approximately 8 to 10 minutes.

For participants receiving coaching sessions, our interventionists tracked the time spent in coaching visits with each caregiver so that we could describe the time required for delivery of that component of the intervention. Website use is tracked via participants’ unique password log-ins to describe the frequency of use, commonly used portions of the website, and patterns of use for participants in both arms of the intervention. The data are presented in the aggregate.

### Fidelity of the Intervention

Throughout the study period, we will randomly select 15 participants randomized to receive coaching sessions. All coaching sessions are observed by an independent expert (with permission from the caregiver). The expert evaluates whether the core topics for each session are presented by the interventionists as outlined in the intervention manual using a checklist (Multimedia Appendix 1). Afterward, the project director analyzes the consistency between the expert and interventionists’ notes (housed in REDCap) using checklists for each session and following a protocol established in previous work [31]. This procedure ensures the robustness and reproducibility of the intervention. Retraining will occur if the agreement between the interventionist and the independent expert falls below 80% (12/15) of the comparisons—to date, our cumulative agreement rate is 100% (5/5). We have successfully used this approach in other caregiver intervention studies [31,77].

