**Figure 2 figure2:**
[figure not shown]
Frequently asked questions for the “caring for yourself” module from the study website.

Participants randomized to the website-coaching group receive (in addition to access to the website) a dose of four personalized coaching sessions (for 6 weeks) from a trained interventionist (licensed independent social worker) who conducts the sessions via videoconference or telephone per each participant’s preference. Completion of these four coaching sessions constitutes a full *dose* of coaching [37]. The four key components of the coaching sessions are (1) session 1—identifying caregivers’ needs for information and support; (2) session 2—strategies for caring for a loved one with multiple sclerosis; (3) session 3—caring for yourself; and (4) session 4—planning and decision-making for the future. The key topics associated with each session are listed in Textbox 1.

Key components of each coaching session.

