Each session uses standardized content but is tailored to focus on issues of relevance to the caregiver. Interventionists follow detailed outlines in the intervention manuals (with links to additional information) in providing skill-building exercises (communication, stress reduction), information, and other topics (evaluating content on the web for accuracy). Outlines were modified as needed by the interventionists based on the caregivers’ assessments. For example, a caregiver who has experience with stress reduction techniques and does not identify high distress will not receive as much depth and detail regarding stress reduction as a caregiver who has little experience with these techniques. Each session takes approximately 35 to 40 minutes based on data from current coaching sessions. The total dose for all four sessions will be 120 to 160 minutes—a dose that reduced caregiver distress and anxiety in previous work [31].

Each participant determined whether their coaching sessions were delivered via telephone or videoconference. For those selecting videoconferences, Zoom (Zoom Technologies, Inc) is the app used for their sessions. We chose this app based on the recommendation of the Case Western Reserve University’s Information Technology department because it provides end-to-end encryption, and we can prohibit invitees from recording videoconference sessions [67]. Caregivers can join Zoom coaching sessions on smartphones, tablets, laptops, or desktop computers.

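### The only stated retraining trigger acts on agreement between the coach's notes and the expert, and no threshold is set on whether the core topics were delivered

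*Protocol article*

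**What the plan says.** All of this is in the protocol article, Methods, chiefly under Fidelity of the Intervention.

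- **Sampling:** "we will randomly select 15 participants randomized to receive coaching sessions", and their coaching sessions are observed.
- **Delivery rating:** "The expert evaluates whether the core topics for each session are presented by the interventionists as outlined in the intervention manual using a checklist".
- **Comparison of records:** "the project director analyzes the consistency between the expert and interventionists’ notes (housed in REDCap) using checklists for each session".
- **Action rule:** "Retraining will occur if the agreement between the interventionist and the independent expert falls below 80% (12/15) of the comparisons".
- **Result so far:** "to date, our cumulative agreement rate is 100% (5/5").
- **Assurance drawn:** "This procedure ensures the robustness and reproducibility of the intervention".

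The Interventions section adds three relevant facts. Coaches may tailor content: "Outlines were modified as needed by the interventionists based on the caregivers’ assessments". There is more than one interventionist, but the number is not given. The project director trained them, retrained during practice where needed, and listened to the first real sessions as a baseline fidelity check. No numeric criterion is given for that check.

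**The concern.** The section collects two different measurements. One is the expert's judgement of whether the core topics were presented, which is delivery fidelity. The other is whether the coach's own notes match the expert's record, which is accuracy of documentation. The threshold and the action are attached only to the second.

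Coaching is the only planned difference between the arms, and the hypothesis rests on it. A rule meant to protect that contrast should respond when core content is dropped. As written, it responds only when the coach and the expert disagree about what happened. The permission to modify session outlines makes this practical: notes that honestly record drift from the manual match the expert just as well as notes that record legitimate tailoring.

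The reported 100% agreement also sits beside the assurance about the intervention, so it is likely to be read as showing that the manual was followed. It does not show that.

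**Working it through.** **1. The article's own figures.** 12/15 = 0.80 and 5/5 = 1.00. Both reproduce. Retraining needs agreement below 80%, so at least 4 of 15 comparisons must disagree; 3 disagreements give exactly 80% and do not trigger.

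**2. What agreement measures.** Let d be the share of comparisons in which the core topics were delivered, and a the probability that the coach's notes are accurate, taken as the same whether or not the topics were delivered. The expert's record is taken as correct.

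Expected agreement = d × a + (1 − d) × a = a.

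Delivery d drops out. With a = 1, agreement is 100% at d = 0.3, 0.5, 0.8 or 1.

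**3. Chance that each rule leads to retraining.** Inputs: 15 comparisons and the 12/15 cut-off (Fidelity of the Intervention). The values of d and a are assumed, and comparisons are treated as independent. P(no retraining) = P(X ≥ 12), where X is binomial with n = 15 and probability a (agreement rule) or d (same cut-off applied to the expert's rating).

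For d = 0.5: (455 + 105 + 15 + 1)/32,768 = 576/32,768 = 0.018, so retraining follows with probability 1 − 0.018 = 0.982.

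| True delivery d | Agreement rule, a = 1 | Agreement rule, a = 0.9 | Cut-off on expert's rating |
|---|---|---|---|
| 0.5 | 0 | 0.056 | 0.982 |
| 0.8 | 0 | 0.056 | 0.352 |
| 1.0 | 0 | 0.056 | 0 |

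Entries are the probability of retraining, one minus the no-retraining values 1.00, 0.944, 0.018, 0.648 and 1.00. The agreement columns are constant in d.

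**4. Where the agreement rule does respond.** If note accuracy differs, with a₁ when topics are delivered and a₀ when they are omitted, expected agreement is d × a₁ + (1 − d) × a₀. A coach who records every topic as covered has a₁ = 1 and a₀ = 0, so agreement = d. The rule therefore detects omissions that are misrecorded and misses omissions that are honestly recorded.

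**5. The interim 5/5.** Even as a measure of agreement, its exact one-sided 95% lower bound is 0.05^(1/5) = 0.549, about 55%.

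**6. Pooling (secondary).** The denominator of 15 equals the whole observed sample and the interim rate is called cumulative, which suggests one figure across coaches. Assuming three coaches with five observed participants each, 5/5 + 5/5 + 2/5 = 12/15 = 80%, so one coach at 40% agreement would not trigger. This illustrates masking of inaccurate notes, not of poor delivery.

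**The case against.** The strongest reply is that the article condenses a fuller procedure. The comparison follows a protocol from earlier work, and an example checklist is in an appendix that is not shown; agreement might be defined there as concurrence that the topics were presented. That lowers certainty about the detail, but it does not change the written rule, which names agreement between coach and expert and sets no mark for the expert's rating.

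A reader might go further and infer the following, which the article does not support:

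- **Poor coaching would go uncorrected.** The project director compares both records and would see an omission noted in each, and also listened to the initial sessions. Correction could follow. What is missing is a stated rule that requires it.
- **The trigger is settled only near the end of delivery.** The cumulative 5/5 shows that the rate is already tracked as data arrive.
- **A null result could not be told apart from under-delivery.** The expert's checklists exist for the observed sessions whatever the trigger says, coaching time is recorded, and a per-protocol analysis is planned. Delivery can be reported afterwards.
- **One weak coach is certainly masked by pooling.** The number of coaches and their share of observed participants are not given, and the rule is worded in the singular. Pooling is an inference.

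It is also fair to say that the quoted assurance refers to the whole procedure, including the expert's observation, and not to agreement alone. A raw count of topics could also penalise tailoring that the article permits, so the fix has to allow for that.

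**Conclusion.** The concern holds in a limited form. The single stated retraining trigger is tied to the accuracy of the notes, while the delivery rating collected in the same observations has no threshold. With fully accurate notes the trigger does not fire at any delivery level; with 90% accurate notes it fires about 6% of the time whatever the delivery. The same cut-off on the expert's rating would fire about 98% of the time at 50% true delivery and about 35% at 80%.

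These figures assume 15 independent comparisons, a correct expert record, and note accuracy that does not depend on whether topics were covered. If coaches record omitted topics as covered, the existing rule does respond. The point bears on protection of the between-arm contrast and on how the fidelity evidence is read. It does not touch the sample size or the primary model, and the pilot's exploratory status limits its weight. It still merits a change, because a better rule is available from data already being collected.

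**What to change.** 1. Apply the existing 80% mark to the expert's checklist rating of core topics presented. A topic covered in less depth because of the caregiver's assessment counts as delivered.
2. Tabulate that rating by interventionist, on the running basis already used for the cumulative rate.
3. Keep agreement between the expert and the notes as a separate check on whether the notes can be trusted.
4. Report both figures, and do not offer the 5/5 agreement as evidence that the manual was followed.

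The cost is one reworded rule and a re-tabulation of checklists that the expert already completes; no new staff or observations are needed. The downside is that reported fidelity may fall below the current 100% and retraining may be more frequent. Counts per coach will also be small, so the running figure for any one coach will be imprecise.
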